### Statistical analysis

All baseline variables will be compared between the control and intervention groups using independent samples t-tests for continuous variables and chi-squared analysis for categorical variables. All outcomes will be reported as descriptive comparisons between the control and intervention groups, with significance reported at alpha = 0.05. Where primary outcomes reach statistical significance, any noted difference in the baseline group comparison will be tested by univariate comparison with stepwise addition into a multivariate model for those with univariate significance of *P *< 0.1. Changes in each group's questionnaire results between baseline and study endpoints, as well as differences between intervention and control group's questionnaire results, will be reported. Further correlational investigations between questionnaire results and adherence will be reported elsewhere. As there are several potential barriers that may prevent a patient randomized to the intervention group from receiving a dHMR according to the protocol, we will use both an intention-to-treat analysis as well as an on-treatment sensitivity analysis.

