### Sample size

We are aiming to detect a change in the primary outcome of 15% between the control and intervention groups. This predicted change is based on the results of the DMACS study, whereby a 12% post-intervention improvement was observed on the proportion of patients taking the same four guideline-based medications at discharge [3]. To detect a change of 15%, assuming a control group result of 45%, a power to detect a difference of 80% with alpha = 0.05, we require a minimum sample size of 186 patients per group. To account for an approximate dropout rate of 20%, we aim to enroll 465 patients in total.

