### Data collection

Baseline data collection will occur in hospital at the time of enrolment, immediately post-discharge from hospital and at six weeks post-discharge - when the participants will be sent their first questionnaire set. The in-hospital baseline data collection will include the recording of traditional coronary risk factors, as well as the 'cholesterol' version of the INTERHEART Modifiable Risk Score (IHMRS) [64]. This will allow for baseline comparison of risk between the two groups. Although not validated to calculate risk in a population of patients following a coronary event, the IHMRS requires the recording of risk factors in a way which emphasizes their correlation to their level of actual risk and this remains relevant, regardless of the patient's degree of heart disease. For example, the IHMRS requires the recording of smoking status into several cutoffs depending on the number of cigarettes smoked per day, which correlates independently to heart attack risk, as opposed to simply recording cigarette smoking status in an arbitrary fashion, which is of lesser value with regard to risk comparisons. The final baseline data collection point of six weeks post-discharge for questionnaire mail-out reflects our intention to gauge each patient's status on each of the questionnaires in the time directly before the HMR and not while in hospital, as factors, such as adherence behavior, may be very high in hospital but may significantly decline over time following discharge [2,3,14,65,66]. Patients in the intervention group will be asked to ensure that they complete their questionnaire before their pharmacist visit and pharmacists will record whether or not this has happened as reported by the patient. Patients in the control group will be given a reminder telephone call if their questionnaires have not been returned by three weeks from the mail-out date.

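### Covariate adjustment is run only after a significant primary result and picks covariates from baseline group differences, so it can confirm or remove an effect but never reveal one

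*Protocol article*

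**What the plan says.** The Statistical analysis section sets out a sequence. First, "All baseline variables will be compared between the control and intervention groups using independent samples t-tests for continuous variables", with chi-squared tests for categorical ones. Outcomes are then compared between the groups, "with significance reported at alpha = 0.05". Adjustment follows only under a condition: "Where primary outcomes reach statistical significance, any noted difference in the baseline group comparison will be tested by univariate comparison with stepwise addition", and entry to the multivariate model is limited to variables with univariate P below 0.1. The section names no covariate, gives no threshold for the stepwise step, plans no adjustment after a non-significant primary result, and does not say whether the unadjusted or the adjusted result decides.

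The Data collection section defines the baseline period widely: "Baseline data collection will occur in hospital at the time of enrolment, immediately post-discharge from hospital and at six weeks post-discharge". Under Randomization, allocation is released at enrolment, once eligibility and consent are entered. The last two of these collection points therefore come after allocation.

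The sample size rests on the unadjusted comparison of two proportions: "assuming a control group result of 45%, a power to detect a difference of 80% with alpha = 0.05".

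**The concern.** Four features of the rule are unsatisfactory.

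1. **The trigger depends on the result.** A significant comparison is re-examined for imbalance; a non-significant one is not, even if imbalance has hidden a real effect.
2. **Candidates are found by testing for chance differences.** Under proper randomisation every baseline difference is a chance difference. A strong predictor of adherence that is balanced never becomes a candidate, although precision is gained from prognostic strength and not from imbalance.
3. **The deciding result is not named.** After adjustment there are two P values for the primary outcome and no rule for a disagreement.
4. **The word baseline reaches past randomisation.** Intervention patients are asked to complete the six-week questionnaire before the pharmacist visit, so they know by then that a visit is coming. Pharmacists only record whether this was done. A six-week difference in, for example, adherence behaviour may partly reflect allocation, and adjusting for it could bias the treatment effect.

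At stake are the interpretation of the primary result and a possible gain in precision at no cost in patients.

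**Working it through.** **Inputs.** From Sample size: control 45%, difference 15 points (45% v 60%), alpha 0.05, power 80%, 186 per group, 20% dropout, 465 in total. Two-sided testing and 1:1 allocation are assumed. The protocol gives no covariate strength, so a range is assumed below.

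**The plan's own figure.** With mean proportion 0.525:

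n = [1.960 × √(2 × 0.525 × 0.475) + 0.842 × √(0.45 × 0.55 + 0.60 × 0.40)]² / 0.15² = 172.8

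With continuity correction: (172.8 / 4) × [1 + √(1 + 4 / (172.8 × 0.15))]² = 185.9, so 186 per group. Then 372 / 0.80 = 465. Both stated figures reproduce. With 186 per group, the uncorrected test has power of about 0.83 by formula and 0.84 by summing the exact binomial probabilities.

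**Chance of a noted imbalance.** Suppose a noted difference means P < 0.05 (the section sets no threshold) and there are k independent variables. The chance of at least one is 1 − 0.95^k: 40% for k = 10, 64% for k = 20 and 79% for k = 30.

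**Simulation of the rule.** 186 per group, 4,000 trials per row. The assumed covariates are 10 or 20 standard normal baseline variables, 3 or 5 of them prognostic. Covariates enter if imbalanced at P < 0.05 and associated with outcome at P < 0.1. The rule counts as positive only if both the unadjusted and the adjusted results are significant. The comparator is a logistic model with the prognostic covariates named in advance. Power is at 45% v 60%.

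| Variables / prognostic / log-OR per SD | Unadjusted | Plan's rule | Prespecified | Overturned | Not looked at |
|---|---|---|---|---|---|
| 10 / 3 / 0.3 | 0.842 | 0.835 | 0.851 | 0.6% | 0.6% |
| 10 / 3 / 0.5 | 0.845 | 0.838 | 0.885 | 0.7% | 1.0% |
| 10 / 3 / 0.8 | 0.839 | 0.831 | 0.916 | 0.8% | 1.5% |
| 20 / 5 / 0.5 | 0.838 | 0.820 | 0.897 | 1.8% | 1.9% |
| 20 / 5 / 0.8 | 0.840 | 0.826 | 0.948 | 1.5% | 2.3% |

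Overturned means significant before adjustment and not after. Not looked at means the reverse, which the rule never examines. The simulation standard error is about √(0.84 × 0.16 / 4,000) = 0.6 points, so the first row shows little gain. With no true effect, type I error is 0.041 to 0.048 under the rule and 0.048 to 0.054 with prespecified adjustment.

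**A single predictor, regimen status.** Assume 60% of patients have a complete regimen at discharge (the Australian study cited in the Background reports 57% and 69%). Two assumed splits both give 45% in controls:

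- Strong: 0.6 × 70% + 0.4 × 7.5% = 45%. Within-stratum variance is 0.6 × 0.21 + 0.4 × 0.0694 = 0.154, against 0.45 × 0.55 = 0.2475, a ratio of 1.61.
- Weaker: 0.6 × 60% + 0.4 × 22.5% = 45%. Variance is 0.6 × 0.24 + 0.4 × 0.1744 = 0.214, a ratio of 1.16.

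In 1,500 simulated trials per case with a 15-point effect, the rule gave 83% power and prespecified adjustment 96% (strong) or 89% (weaker). With a true effect of 12 points the figures were 62% against 83% or 69%.

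**Where the effect falls.** A further 20,000 trials per case used a test stratified on regimen status, against 84% unadjusted, with a 15-point overall effect:

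| Location of effect | Strong split | Weaker split |
|---|---|---|
| Incomplete-regimen patients only | 90% | 84% |
| Common odds ratio | about 97% | about 88% |
| Complete-regimen patients only | 99% | 92% |

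At the planned effect, the gain therefore runs from none (84% to 84%) to about 15 points (84% to 99%).

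**The case against.** An unadjusted comparison of two proportions is a legitimate primary analysis, the trial is sized for it, and its power exceeds the planned 80%. A reader might infer that the rule wastes power the trial needs. The documents do not support that: what is lost is an optional gain, and its size rests on covariate strengths that the protocol does not give.

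A reader might also infer that the rule inflates false positives or often destroys true ones. It does neither. Requiring both results to be significant cannot raise the error rate, and overturning occurs in only 0.6% to 1.8% of simulated trials with a true effect.

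Nor does the text say that the adjusted model replaces the unadjusted result, so it cannot be said that the final estimate comes from a data-chosen model. The text is silent, and an analysis plan not shown may settle the matter.

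The univariate screen at P < 0.1 is most naturally read as association with outcome, so prognosis is not disregarded. But it is applied only to variables already picked for imbalance, so a balanced strong predictor still stays out. Regimen status at discharge is not ignored either: under Primary outcome, a secondary analysis is planned in patients discharged on a complete regimen. That analysis does not adjust the main comparison.

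Finally, the Statistical analysis section treats questionnaire results in a separate sentence, and they are intended to precede the pharmacist visit. That they would enter the model is therefore a possibility left open by the wording, not a stated intention.

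What remains is that the protocol itself fixes the trigger and the way candidates are selected. They are not details left to another document.

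**Conclusion.** The point holds as an improvement to a stated rule. Adjustment conditional on significance, with candidates taken from baseline tests, is one-directional and leaves the deciding result undefined. As worded, it could also admit variables measured after allocation. Neither the planned power nor the type I error is harmed.

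The forgone gain at the planned 15-point effect ranges from almost none to roughly 10 to 15 points. It rests on assumed covariate strength, on an assumed 60% with a complete regimen, and on where the effect falls. The direction is firm, the size is not. The chance-imbalance figures assume independent variables and a 0.05 threshold.

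**What to change.** In the Statistical analysis section:

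- Delete the significance trigger, the choice of covariates by baseline P value, and the stepwise selection.
- Prespecify one adjusted primary analysis, run whatever the unadjusted result, with arm, hospital, age and guideline-regimen status recorded before randomisation. Use regimen at discharge only if it is settled before allocation.
- Name that analysis as decisive and report the unadjusted comparison as supportive.
- State that six-week questionnaire variables may not be used as covariates.

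Recruitment has not started, so this is mainly a change of wording, and the sample size can stand. There are two small costs. The covariates must be fixed in advance. Regimen status at enrolment is not among the in-hospital items named under Data collection, so it must be confirmed as a recorded baseline item or added.

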## Methods/Design

### Overview

We will conduct a randomized controlled trial comparing the dHMR service delivered at two months post-discharge to usual care following an ACS admission. Changes in the pharmacist referral process and an ACS-specific education package to be completed by the study pharmacists make this program different to the standard HMR service. The primary outcome will be the proportion of patients who are adherent to a complete, guideline-based ACS medication regimen at six and twelve months post-discharge. Patients will be enrolled in hospital during an admission for ACS. Figure 1 provides an overview of the trial protocol. The design of the intervention and monitoring system has been based on a conceptual framework for the standardized evaluation of chronic disease management interventions, as developed by Lemmens *et al. *[28]. Figure 2 is a summary of this framework and Figure 3 is a comparison of how the components of this trial compare against the Lemmens *et al. *framework.

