### Outcomes

All outcomes will be measured using blinded assessment processes at the two study endpoints of six and twelve months post-discharge. Each outcome will be a comparison between the control and intervention groups. A proposed conceptual framework for the standardized evaluation of chronic disease management interventions has been considered in the selection of the trial outcomes and further trial evaluation [28]. Using a framework to guide outcome selection has not only helped to ensure that we are measuring the important clinical outcomes from the intervention, but also highlighted the individual steps of the intervention that require monitoring. Monitoring these individual steps, such as pharmacist detection of drug-related problems and GP acceptance of pharmacist recommendations, is important to measure the level of alignment between the theoretical plan and the practical application of the intervention. Such detailed monitoring and outcome reporting may also elucidate areas of practice worthy of further focus in future research.

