### Secondary outcomes

Secondary outcomes will include hospital readmission rates, length of hospital stays, changes in quality of life, cardiac rehabilitation completion rates, smoking cessations rates, and mortality. Hospital readmissions and mortality will be further categorized as ACS-related or due to other causes. Quality of life will be measured at six weeks post-discharge as a baseline, pre-dHMR measure and again at both study endpoints. The Euroqol 'EQ-5D 3 L' [42] will be used to measure general quality of life and the Seattle Angina Questionnaire (SAQ) [43] will be used to measure cardiac-specific quality of life. Both instruments have been validated when administered individually [43-46] and in combination [47] to assess quality of life in patients with coronary heart disease. In addition to a self-report of smoking status at baseline and the study endpoints, we will be further categorizing each smoker's dependence on cigarette smoking using the Fagerstrom Test for Nicotine Dependence (FTND) [48].

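### Quality of life and the other questionnaire scores are summarised by change and by group difference, with no planned adjustment for the six-week score, which gives up some precision in secondary and process outcomes

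*Protocol article*

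**What the plan says.** The handling of questionnaire results is given in one sentence of the protocol article, under Statistical analysis: "Changes in each group's questionnaire results between baseline and study endpoints, as well as differences between intervention and control group's questionnaire results, will be reported". The same section says of every outcome: "All outcomes will be reported as descriptive comparisons between the control and intervention groups, with significance reported at alpha = 0.05". Adjustment appears once, and only for the primary outcome: "Where primary outcomes reach statistical significance, any noted difference in the baseline group comparison will be tested by univariate comparison", with variables then added stepwise to a multivariate model.

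The data for an adjusted analysis will be collected. Under Secondary outcomes: "Quality of life will be measured at six weeks post-discharge as a baseline, pre-dHMR measure and again at both study endpoints". Under Data collection, the six-week mail-out of the questionnaire set "reflects our intention to gauge each patient's status on each of the questionnaires in the time directly before the HMR". The Outcomes section makes clear that a treatment comparison is intended: "Each outcome will be a comparison between the control and intervention groups".

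Two statements qualify the word baseline. Under Overview, "Patients will be enrolled in hospital during an admission for ACS", and the Randomization section allocates patients once eligibility and consent are entered. The six-week score therefore follows randomisation. Under Data collection, "Patients in the intervention group will be asked to ensure that they complete their questionnaire before their pharmacist visit", and the pharmacist records whether this happened. Completion before the visit is requested and recorded, not guaranteed.

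**The concern.** The trial plans a measurement of each scale shortly before the intervention, but the stated analysis does not use it in the most efficient way.

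- **Change within a group** is not a treatment comparison. Recovery after the acute event and regression to the mean would move both arms.
- **The difference between groups at an endpoint** is a valid randomised comparison, but it leaves the six-week score unused.
- **Change compared between arms**, if that is how the two summaries are combined, carries the full noise of the six-week score.

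At stake is the width of the confidence intervals for EQ-5D, the Seattle Angina Questionnaire (SAQ) and the patient-process scales. Intervals wider than the data require make it more likely that a real effect of the dHMR on quality of life, beliefs or self-efficacy is missed. Validity is not at stake, and neither is the primary outcome.

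**Working it through.** **The plan's own figure.** The only sample size in the article is for the binary primary outcome (Sample size section: 45% in controls, a 15-point difference, 80% power, alpha 0.05). A two-sided two-proportion calculation for 45% against 60% gives 173 per group without continuity correction and 186 with it, which matches the article. With 20% dropout, 2 × 186 / 0.8 = 465, which also matches. No SD, effect size or correlation is given for any questionnaire, so these figures serve only as a reference size below.

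**Variances.** Assume the same SD at six weeks and at the endpoint, and correlation rho between them. Relative to one endpoint score, the large-sample variance of the between-arm difference is:
- endpoint only: 1
- change score: 2(1 - rho)
- adjusted for the six-week score: 1 - rho²

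The adjusted variance is below 1 whenever rho is not 0. Its ratio to the change-score variance is (1 - rho²) / [2(1 - rho)] = (1 + rho)/2, which is below 1 whenever rho is below 1. The endpoint difference is the better of the other two below rho 0.5, the change score is better above it, and they tie at 0.5.

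**Power.** Take an effect that the better of the two detects with 80% power at two-sided alpha 0.05, so that the standardised signal is 1.960 + 0.842 = 2.802. Adjustment divides this by the square root of the variance ratio, and power is Φ(2.802/√ratio - 1.960). Rho is an assumption, shown over a range.

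| rho | endpoint | change | adjusted | better of first two | ratio adjusted/better | power after adjustment | gain (points) |
|---|---|---|---|---|---|---|---|
| 0.3 | 1 | 1.40 | 0.91 | endpoint | 0.91 | 83.6% | about 4 |
| 0.5 | 1 | 1.00 | 0.75 | equal | 0.75 | 89.9% | about 10 |
| 0.7 | 1 | 0.60 | 0.51 | change | 0.85 | 86.0% | about 6 |
| 0.8 | 1 | 0.40 | 0.36 | change | 0.90 | 84.0% | about 4 |

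Example at rho 0.5: 2.802/√0.75 = 3.235, and Φ(3.235 - 1.960) = Φ(1.275) = 0.899.

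Because power is anchored at 80%, the gain does not depend on the number of returned questionnaires. For scale only, with 186 per arm the endpoint comparison has 80% power at 2.802 × √(2/186) = 0.29 SD.

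**Against the less precise summary** the gain is larger. At rho 0.3 the change score goes from 80% to 93.5%. At rho 0.7 the endpoint difference goes from 80% to 97.5%. Both summaries are reported, so the better one is the fair comparator.

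**A difference already present at six weeks.** The change score subtracts all of it. With equal SDs the regression slope is rho, so the adjusted analysis subtracts about rho times it. The endpoint difference subtracts none.

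**The case against.** The strongest objection is that the article only says what will be reported. The words raw and unadjusted do not appear, and a statistical analysis plan that is not shown could specify a baseline-adjusted model. This stands in part: the article does not exclude adjustment. It does, however, name the summaries, call the comparisons descriptive, and describe adjustment for primary outcomes alone. Using the six-week score as a covariate is thus a better method than the one described, not merely a missing detail.

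A reader might infer that the plan tests raw change between arms, or tests change within each arm. The documents support neither as a stated plan. The Statistical analysis section lists change in each group and difference between groups. A between-arm test of change is plausible, because Secondary outcomes lists changes in quality of life, but it is not written down.

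A reader might also treat the six-week score as a true pre-treatment baseline. It follows randomisation, and the Discussion has the enrolling researcher contact the GP once allocation is known. Some intervention patients may return the form after the visit. Control patients get a reminder call three weeks after mail-out, about nine weeks after discharge, close to the planned time of the dHMR. Adjustment could therefore remove part of an early effect. The change score shares this weakness to a greater degree, but the unadjusted endpoint difference does not have it. This objection stands and shapes the fix.

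Finally, one linear model does not suit every instrument. The four-item self-report adherence scale and recall of medication purpose are short ordinal or binary measures. This also stands.

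**Conclusion.** The point holds as a modest loss of precision in secondary and process outcomes. Its direction is certain for any rho strictly between 0 and 1, given equal SDs at the two times. Its size rests on rho, which the protocol does not give. Over rho 0.3 to 0.8, the gain over the better of the two summaries is about 4 to 10 points from 80% power. A gain of 10 points over both summaries holds only at rho 0.5 and should not be read as typical.

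It would go too far to call the described analysis biased or invalid: the endpoint difference between randomised groups is sound, only less efficient. The primary outcome, the 186 per group and the total of 465 do not change.

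**What to change.** Amend the questionnaire sentence under Statistical analysis as follows.

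- **Main comparison.** For EQ-5D, SAQ and the other approximately continuous scores, compare the six- and twelve-month scores between randomised groups in a linear model with the six-week score of the same instrument as covariate. Report the adjusted difference with its 95% CI.
- **Within-group change.** Present it as description only.
- **Sensitivity analysis 1.** Keep the unadjusted endpoint difference alongside. It uses every returned endpoint form and retains any effect that arose between randomisation and six weeks.
- **Sensitivity analysis 2.** Repeat the adjusted analysis without six-week forms recorded as completed after the dHMR. These exclusions fall in the intervention arm only, so this should not become the main analysis.
- **Short ordinal or binary measures**, such as the four-item adherence scale and purpose recall: use a model suited to the scale.

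The cost is analysis wording and two additional analyses, with no new data, visits or patients. The Trial status section says recruitment has not started. The small downside is that patients without a six-week form drop out of the adjusted model, as they already do from the change score. They remain in the unadjusted comparison if they return an endpoint form.
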